## Abstract

**Background:**

Guidelines recommend a biopsychosocial framework for low back pain (LBP) management and the avoidance of inappropriate imaging. In clinical practice, care strategies are often inconsistent with evidence and guidelines, even though LBP is the most common disabling health condition worldwide. Unhelpful beliefs, attitudes and inappropriate imaging are common. LBP is understood to be a complex biopsychosocial phenomenon with many known multidimensional risk factors (symptom- and lifestyle-related, psychological and social) for persistent or prolonged disability, which should be identified and addressed by treatment. The STarT Back Tool (SBT) was developed for early identification of individual risk factors of LBP to enable targeted care. Stratified care according SBT has been shown to improve the effectiveness of care in a primary care setting. A biopsychosocially-oriented patient education booklet, which includes imaging guidelines and information, is one possible way to increase patients’ understanding of LBP and to reduce inappropriate imaging. Premeditated pathways, education of professionals, written material, and electronic patient registry support in health care organizations could help implement evidence-based care.

**Methods:**

We will use a Benchmarking Controlled Trial (BCT) design in our study. We will prospectively collect data from three health care regions before and after the implementation of a classification-based approach to LBP in primary care. The primary outcome will be change in PROMIS (Patient-Reported Outcomes Measurement Information System) (short form 20a) over 12-month follow-up.

**Discussion:**

The implementation of a classification-based biopsychosocial approach can potentially improve the care of LBP patients, reduce inappropriate imaging without increasing health-care costs, and decrease indirect costs by reducing work disability. Using the BCT we will be able to evaluate the effectiveness of the improvement strategy for the entire care pathway.

**Trial registration:**

**ISRCTN,**ISRCTN13273552, retrospectively registered 13/05/2019.

## Background

Guidelines recommend biopsychosocial frameworks for low back pain (LBP) management and avoidance of inappropriate imaging [1–3]. In clinical practice, care strategies are not always aligned with evidence and guidelines even though LBP is the most common disabling health condition worldwide [4, 5]. Unhelpful beliefs, attitudes and inappropriate imaging are common [6, 7]. A specific cause of pain can only be found for a small percentage of LBP patients, and over 90% are classified as having non-specific pain [8]. LBP is a complex condition in which biological, psychological, and social factors impact on both the experience of back pain and the associated disability [3, 9]. Risk factors for poor prognosis of LBP include high pain intensity, adverse subjective belief of long-lasting pain, low self-efficacy (i.e. confidence in one’s own ability to get on with life despite the pain), passive coping strategies, high catastrophizing and fear avoidance beliefs, depression, sleep problems, psychological distress, low education and social class, and unemployment [3, 4, 10–12].

In addition to patient-related factors and management, professional and health care system-related factors also affect the outcomes of patients with LBP. Such factors include imaging policy, patient education, the attitudes and beliefs of health care professionals, and the timing of rehabilitation [2, 13, 14].

Imaging findings of degeneration of the lumbar spine are also prevalent among asymptomatic adults [15, 16]. Imaging of LBP patients without indications of serious underlying conditions does not improve clinical outcomes [17]. On the contrary, early magnetic resonance imaging (MRI) may be even harmful for LBP patients [18, 19]. Early MRI is associated with additional examinations, injections, operations, and increased health care utilization and costs [20, 21]. Adding epidemiologic data to MRI reports may decrease specialist consultations, repeated imaging and narcotics prescriptions, whereas no effect has been shown on the rate of operations and injections [22, 23]. Comprehensive evidence-based information on LBP is more beneficial than imaging. Patient education based on the biopsychosocial model has shown to be an effective strategy for modifying beliefs about LBP, minimizing its consequences and improving treatment compliance [24, 25]. Appropriate patient education can reduce pain and disability in the short term [26]. Even simple patient information has shown to be cost-effective and to produce savings in the costs of managing mild low back symptoms in occupational settings [27].

Practitioners’ beliefs affect how they explain pain to the patient and what kind of care they choose [28, 29]. Non-pharmacological treatment considering psychosocial factors is not given, as LBP guidelines and evidence suggest, if the attitudes and beliefs of the treating physician are biomedical [30]. It also matters which type of health care professional first sees the patient. Direct access to a physiotherapist (PT) reduces waiting times, improves outcomes through earlier access to care, prevents acute problems becoming chronic, reduces long-term pain and disability, and decreases time off work [14, 31]. Direct access to a PT has resulted in high satisfaction among both patients and PTs [14]. In Finland, direct access to a PT due to musculoskeletal symptoms has been observed to reduce the number of general practitioner (GP) visits, with only 4% of patients with direct PT access being referred to a GP [32].

Treatment of LBP should address the complexity of biological, psychological and social factors [33]. The risk of prolonged disability due to pain varies among patients, which can be seen during the first health care visit [34, 35]. Standardized questionnaires can be used for risk identification because professionals’ ability to identify psychosocial risk factors is limited even if they have been trained [36]. The STarT Back Tool (SBT) questionnaire allocates LBP patients to low-, medium- or high-risk groups of persistent disabling back pain [37]. The SBT has been validated in Finnish [38]. Using the SBT as a screening method for the classification-based approach has shown to improve the effectiveness of LBP treatment in primary care [37]. Successful use of a classification-based approach using SBT as a screening method has shown significant improvements in patient disability outcomes, halving time off work without increasing health care costs [39]. On the other hand, if its implementation has been deficient or unfeasible, no effects have been found [40].

In order to be able to provide evidence-based care, it is essential that health care organizations ensure that the correct options are feasible for professionals by, for example, providing them with sufficient knowledge and training [41] and systematically identifying patients’ individual risk factors^35.^ Using classification-based care pathways may enable the optimization of patients’ treatment and the use of limited health care resources. Written local policy information, support of electronic patient registry functions, education of professionals, successful co-operation between professionals, and a patient education booklet supporting evidence-based care could all enhance the implementation and effectiveness of classification-based care for LBP in primary care [42, 43]. Applying a classification-based approach throughout the care pathway is likely to present a major opportunity to enhance cost-effectiveness of LBP treatments in primary care and hence reduce LBP-related disability.

We hypothesize that a classification-based approach, which includes providing the correct information and a new means for professionals to assess and treat LBP patients according to their individual risk profile, will optimize the treatment of patients as well as the use of health care resources. We further assume that the classification-based approach will be effective and save costs in comparison to current best practice.

### Objectives

The aim of this study is to investigate whether the classification-based approach to LBP patients and the education of professionals in primary care improves patients’ functional ability and quality of life and reduces work disability in both the short (over the first 3 months) and long term (over the first year). Furthermore, we aim to evaluate the cost-effectiveness of this approach in comparison to current best practice, using direct costs such as visits to health care professionals, referrals to MRI, and pain medication; and indirect costs such as sick leaves and disability pensions. A secondary objective is to evaluate whether education can change professionals’ attitudes towards LBP and its treatment by following their attitudes, beliefs and satisfaction related to the treatment process.

### Trial design

We will use the Benchmarking Controlled Trial (BCT) as our study design [44]. The BCT enables the evaluation of differences in effectiveness between clinical pathways and complex interventions targeting health care system factors [45]. It also documents and takes into consideration the characteristics of regional health care systems or organizations.

## Methods/ design

### Study setting

We have selected three primary health care regions for the study, which are described in Table 1. First, ESSOTE (Etelä-Savon sosiaali- ja terveyspalvelut, The South Savo social and health care authority), which consists of the city of Mikkeli (population approx. 54,000) and smaller areas around Mikkeli (Hirvensalmi, Mäntyharju, Puumala, Juva, Pertunmaa, Kangasniemi) and has been one joint health care region since 2017. Second, EKSOTE (Etelä-Karjalan sosiaali- ja terveyspiiri, South Karelia social and health care district), which is a joint municipality authority of the South Karelia region, and comprises nine municipalities: Lappeenranta, Lemi, Luumäki, Imatra, Parikkala, Rautjärvi, Ruokolahti, Savitaipale, and Taipalsaari. Of these, the city of Lappeenranta is the largest, with approximately 72,000 inhabitants. Rovaniemi city is the study’s third health care region and contains four health care centres: Pulkamontie, Urheilukatu, Metsäruusuntie and Rinteenkulma (population covered approx. 62,000). All general physicians and PTs in the study’s health care centres will be invited to participate in the study. The patients will be recruited by health care professionals during their normal appointments.

**Table 1 Tab1:** Statistics of health care regions

			Public Health Care		Occupational Health Care Enterprises	
Region	Population	18–64-year-olds (%)	Physicians (N)	Physiotherapists (N)	Physicians (N)	Physiotherapists (N)
ESSOTE	79,808	57.2	36	12	18	13
EKSOTE	131,764	58.6	58	28	10^a^	5^a^
Rovaniemi	62,420	64.9^b^	35	10	***	***

ESSOTE (Etelä-Savon sosiaali- ja terveystoimi, The South Savo social and health care authority), EKSOTE (Etelä-Karjalan sosiaali- ja terveyspiiri, South Karelia social and health care district)

^a^The figures include only those working in EKSOTE’s own occupational health service organization; there are four other occupational health service organizations in the South Karelia county. ^b^15–64-year-olds. (http://tilastokeskus.fi/index.html). ***No occupational health services involved in the study

### Eligibility criteria

All patients aged 18–65 who contact health care due to LBP, either with or without radicular pain, will be included in the study. Exclusion criteria are: 1) Age under 18 or over 65; 2) First patient-reported contact with health care due to LBP and episode lasting less than 2 weeks; 3) Suspicion of a serious cause of LBP or LBP requiring urgent care. Patients will receive written information on the study. Only patients who sign the consent form will be included in the study.

### Intervention

The intervention implements the classification-based biopsychosocial approach to LBP patients in primary care. Table 2 describes the elements of implementation. We will use the SBT for classification. The SBT consists of eight items (or themes): bothersomeness, referred leg pain, comorbid pain, disability (two questions), catastrophizing, fear, anxiety, and depressive symptoms. The response alternatives to Items 1–8 are “agree= 1 point” or “disagree = 0 point”. Item 9 has five options, of which the two highest responses will be counted as one point. Thus, the maximum total score range will be 0–9. In addition, the psychosocial subscale will be derived from Questions 5–9 (range 0–5). The following risk groups will be formed: 1) Low-risk (total score of 3 or less); 2) Medium-risk (total score of 4 or more and psychosocial subscale score of 3 or less); and 3) High-risk (total score and psychosocial subscale score of 4 or more) [39].

**Table 2 Tab2:** Elements of implementation

Level of element	Implementation elements of a classification-based biopsychosocial approach
Organizations	Premeditated care pathways for LBP patients
	More resources targeted towards high-risk patients
	Support of electronic patient registry functions
Professionals	Education: Physicians 4 h, physiotherapists 4 days, nurses 2 h, short booster education sessions in units
	SBT used systematically
	Patient education booklet in use
	Premeditated phrases (and SBT) for nurses
	Referral to physiotherapy according to risk classification
Patients	SBT
	Patient education booklet
	Individual biopsychosocially-oriented care

*LBP* Low Back Pain, *SBT* STarT Back Tool

#### Organizational level

We will evaluate all the possible pathways for the patients with LBP in each health care region. Direct access to a PT will be emphasized. For nurse appointments, premeditated phrases will be taught and integrated into the electronic patient record system. Local practices within each health care region will be modified to enable easy access to care according to risk classification. Local practitioners and managers such as the clinical director of the GPs, the nurse manager in primary care, and the manager of the PTs will be involved when modifying the pathways according to regional specific facilities and resources. All the health care professionals involved in the LBP patients’ care will be informed of the new care pathways. Education on the new strategies will be organized for professionals and written information will be given to each health care region. Figure 1 shows the aim of the care pathway and the detailed strategies for achieving it will be locally planned for each health care region. Table 3 describes the health care region-specific challenges and strengths during the implementation process. Co-operation between public health care and occupational health service organizations will be enhanced through joint education (not possible in Rovaniemi).

**Fig. 1 Fig1:**
[figure not shown]
Aim of care pathway

**Table 3 Tab3:** Health care region-specific challenges and strengths during implementation process

Health care region	Challenges	Strengths
ESSOTE	A simultaneous extensive organizational change (fusion of primary and secondary health care organizations, including relocation of primary care facilities)	Research nurses and the principal investigator can remind/educate professionals of the new protocol from time to time. During the re-evaluation, additional education lessons will take place in units during • emergency duty nurses’ meeting 2x60min • student health care unit nurses’ meeting 1x90min • junior physicians’ meeting 1x75min • GPs’ meeting 1x60min • general medicine department nurses’ meeting 2x30min • PTs’ meeting 2x30min • occupational health physicians’ meeting • PTs’ meeting 1x60min The nurse in charge of the emergency room is active in improving the implementation of the new care strategy.
Rovaniemi	Low GP participation rate in education. Emergency department not part of the study. Simultaneous relocation of primary health care facilities. No occupational health service organization included the study.	Previously complicated wide criteria for direct access to PT enormously reduces the possibility to use it. A notable criterion for direct access to physiotherapy during implementation process might be helpful.
EKSOTE	Simultaneous change in electronic medical record system increases requirements to adopt new working practices among professionals.	Some biopsychosocial oriented education for PTs had been held before this study, which is helpful for implementation. Mentoring will be arranged for PTs during implementation and re-evaluation.

ESSOTE (Etelä-Savon sosiaali- ja terveystoimi, The South Savo social and health care authority), EKSOTE (Etelä-Karjalan sosiaali- ja terveyspiiri, South Karelia social and health care district)

#### Professional level

We will improve the implementation of the classification-based approach by educating professionals (nurses, PTs, physicians). The education seminar programmes are available in the supplementary information. Education will improve the implementation of the new care strategy and aims to enable professionals to equally transfer correct information from health care to all patients. The education will be provided by Professor of Physiatry, [name]; [name], Specialist in General Medicine; [name], Physiotherapist, MSc; [name], OMT Physiotherapist; and [name], Occupational Physiotherapist. [name] is a specialist in Physical and Rehabilitation Medicine and has published over 200 peer-reviewed papers on musculoskeletal problems, including randomized controlled interventions among LBP patients. [name] is an experienced clinician in the field of pain and has wide-ranging practical knowledge of health care services and organizations. All the trainers are experienced in using and teaching the biopsychosocial approach.

The PTs will receive 4 days (28 h) of education in biopsychosocially-oriented individualized physical therapy and classification-based care. The training will carefully cover the physiology of LBP from the biopsychosocial perspective, evidence-based care, and low value care. The main messages of the training will include a biopsychosocial explanation for pain, therapeutic alliance, validation and avoidance of invalidation, avoidance of unhelpful/harmful messages and unnecessary imaging in non-specific LBP. It will also contain an assessment of individual psychosocial factors (using SBT and the short version of Örebro Musculoskeletal Pain Screening Questionnaire) and individualized care plans in accordance with the risk classification, and demo patients’ cases. Listening and interaction will be highlighted. In the EKSOTE region, the PTs willing to treat high-risk patients will receive an extra half day of group training and personal mentoring for at least 3 months. Mentoring will include discussions in groups/pairs, accompanied by patient appointments of a colleague and goal-directed learning tasks related to their own work and clinical patients.

For physicians, we will provide a four-hour education session. Its four main themes will be: imaging issues, SBT, lifestyle factors, and work disability. We will discuss the relevance of lumbar MRI findings, such as the prevalence of findings among asymptomatic adults and the disadvantages of imaging. We will also teach key pain medication issues. The role of physiotherapy will be emphasized. The physicians will also be taught the main principles of biopsychosocially-oriented individualized care.

For the nurses we will conduct two two-hour sessions, which will include data on the natural course of LBP, the harm of nocebo messages that health care providers give patients, risk classification using the SBT and the current treatment principles and pathways. Premeditated phrases in electronic medical records will enhance patient history clarification and classification-based care guidance.

The professionals will systematically use the SBT with all their LBP patients and will make individual care plans for patients according to their risk profile. A patient education booklet, based on the biopsychosocial model, will be used to deliver evidence-based information on the aetiology of LBP and appropriate imaging to patients. It will also remind professionals of the biopsychosocial LBP model. The booklet has been validated and translated into Finnish ([name] et al. submitted).

#### Patient level

All the LBP patients will receive the patient-education booklet. They will be classified into low-, moderate- or high-risk groups during their first visit to primary health care, based on the SBT. The physicians and PTs will use the SBT as a classification method during the LBP patient’s visit. The physicians and PTs will plan the individual treatment process according to the risk classification.

Low-risk patients will receive advice on how to stay active including advice on pain medication, if appropriate. The patient education booklet will be based on the biopsychosocial model. Referral to a PT will only be scheduled when necessary.

Medium-risk patients will receive the same care as the low-risk group. However, all medium-risk patients will also be referred to physiotherapy. In addition to the clinical examination and patient advice, the PTs will evaluate their patients’ pain, fears and maladaptive behaviours. Physiotherapy will be individualized and at least one follow-up PT visit will be recommended. Each patient will have approximately two to 4 PT visits, but an individualized approach to care will be highlighted, so that exceptions can be made in each individual care plan. Co-existing symptoms will be evaluated and treated if needed. In cases of sleep problems, the patient will be referred to a sleep management group or individual guidance with a focus on non-pharmaceutical treatments, or to a psychiatric nurse in the health centre if needed. Other co-morbidities such as smoking, overweight and type 2 diabetes will be taken into consideration and the patient will be referred for further care if needed.

High-risk patients will receive a similar treatment protocol to medium-risk patients, but with an emphasis on psychosocial factors and with as short a delay a possible before starting physiotherapy (less than 1 week). Faster access to physiotherapy will be arranged using premeditated pathways for high-risk patients.

### Primary outcome measure

The primary outcome will be change in PROMIS PF-20 (Patient-Reported Outcomes Measurement Information System) (short form 20a) from baseline to 12-month follow-up. A translated and validated Finnish version of the PROMIS PF-20 will be used [46, 47].

### Secondary outcome measures

Pain and disability: change in PROMIS PF-20 from baseline to three-month follow-up; change in Oswestry Disability Index (ODI) from baseline to 3- and 12-month follow-up; change in SBT from baseline to 12-month follow-up.

Health-related quality of life: change in EQ-5D (EuroQol five dimensions) from baseline to 12-month follow-up.

Direct and indirect costs will be measured over the 12-month follow-up period, and will include:
Direct costs: Physician visits, PT visits, nurse visits, other health care clinician visits (e.g. psychologist), imaging due to LBP (x-ray/MRI/CT (computer tomography)), pain medication, and surgical and other invasive interventions.Indirect costs: Days on sick leave (LBP-related and all sick leaves).

Details on prescription medicine reimbursements, as well as details on sick-leave payments are available from the nationwide registers maintained by the Social Insurance Institution of Finland (SII, Kela in Finnish). These should provide, to the nearest cent (¢), the costs paid by the health care sector in Finland for these two cost drivers. For the costs of visits to publicly provided health care we intend to use the information that the Finnish Institute for Health and Welfare (THL) gathers from Finnish hospitals, available from the Care Register for Health Care (CRHC). Secondary outcomes are described in Table 4.

**Table 4 Tab4:** Secondary outcomes

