**Indirect costs**	
Days on sick leave during last year (LBP-related and all sick leaves)	
Disability pensions during first year	

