### Statistical methods

Baseline characteristics will be analysed using descriptive statistics. The change in each outcome from baseline to the follow-up visits in the intervention regions and the differences between the intervention regions and control regions will be analysed using a range of statistical methods, including univariate and multivariate techniques. SPSS Statistics (version 25) will be used for statistical analyses. For the cost-effectiveness analysis we will use the health care resource questionnaires described earlier. Health care resource use will be calculated as the number of visits multiplied with the unit cost per item and expressed as mean costs by items of resource use and the mean direct total health care resource costs. All costs will be discounted to the price level of the most recent follow-up year.

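### The listed cost items leave out the cost of delivering the intervention, so the before/after cost difference would not be net of it and could not support a savings claim

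*Protocol article*

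**What the plan says.** In the protocol article, the Background hypothesis expects the approach to be effective and cheaper than current best practice. Objectives then promises a cost-effectiveness comparison using direct costs, given by example, and "indirect costs such as sick leaves and disability pensions".

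Secondary outcome measures states: "Direct and indirect costs will be measured over the 12-month follow-up period, and will include". The direct list begins "Direct costs: Physician visits, PT visits, nurse visits, other health care clinician visits (e.g. psychologist), imaging due to LBP" and ends with pain medication and invasive procedures. The indirect list is "Indirect costs: Days on sick leave (LBP-related and all sick leaves"). Table 4 repeats these items and adds "Disability pensions during first year".

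Statistical methods multiplies the number of visits by a unit cost, with results "expressed as mean costs by items of resource use and the mean direct total health care resource costs". It adds: "All costs will be discounted to the price level of the most recent follow-up year".

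The intervention uses staff time of its own. Under Professional level: "The PTs will receive 4 days (28 h) of education in biopsychosocially-oriented individualized physical therapy". Physicians get one four-hour session. Nurses get two hours according to Table 2, or two sessions of two hours according to Professional level. Table 2 adds booster sessions. EKSOTE physiotherapists who take on high-risk patients get a further half day and at least three months of mentoring. All patients get a booklet.

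Participant timeline compares each region before and after implementation, which comes about one year after the baseline evaluation.

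**The concern.** In a before/after comparison within the same regions, training, mentoring and booklets are spent only to produce the after condition. A cost comparison that values patients' visits, imaging, medication and surgery, but not these inputs, credits the new approach with any reduction in use and does not charge it for what the reduction took to achieve. The resulting difference answers whether patients used fewer services. It does not answer whether the approach saved money, which is what the hypothesis asserts. The data also matter: training attendance and mentoring time are easy to log as they happen and hard to reconstruct later.

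**Working it through.** **1. Does any stated item or data source capture delivery?**

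| Resource | Listed cost item? | Captured by visits x unit cost? |
|---|---|---|
| Extra physiotherapist, nurse or other clinician visits | Yes | Yes |
| Imaging, medication, surgery | Yes | Separate items or register amounts |
| Training of physiotherapists, physicians, nurses | No | No, not a patient visit |
| Boosters and EKSOTE mentoring | No | No |
| Trainer time, booklets | No | No |

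The data tables do not fill the gap. Table 5 collects appointments, imaging and secondary-care consultations at organizational level. Table 6 asks professionals whether they use the education leaflet, but not about hours trained. Table 7 is the patient questionnaire. In addition, costs are counted over each patient's 12-month follow-up, whereas implementation precedes the re-evaluation, so the main training lies outside the costed window.

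**2. Staff hours (counts from Table 1, hours from Professional level).** The plan states no figure to reproduce.
- Public physicians: 36 + 58 + 35 = 129. Occupational health: 18 + 10 = 28. Total 157.
- Public physiotherapists: 12 + 28 + 10 = 50. Occupational health: 13 + 5 = 18. Total 68.
- Public staff only: 129 x 4 + 50 x 28 = 516 + 1,400 = 1,916 h.
- All staff: 157 x 4 + 68 x 28 = 628 + 1,904 = 2,532 h.

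The larger total is an upper bound for physician and physiotherapist training: it assumes full attendance, and Table 3 notes low GP participation in Rovaniemi. Nurses (number not given), boosters, mentoring, trainers and booklets would be added.

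**3. Money.** The article gives no wage, attendance or patient count. Assume EUR 25-60 per hour and 25-100% attendance.
- Low: 1,916 x 0.25 x 25 = EUR 11,975.
- High: 2,532 x 1.00 x 60 = EUR 151,920.

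Per patient, by denominator:
- Assumed 3,000 low back pain patients seen: 11,975 / 3,000 = EUR 4; 151,920 / 3,000 = EUR 51.
- Study patients after implementation only, 340 / 2 = 170: 11,975 / 170 = EUR 70; 151,920 / 170 = EUR 894.

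Training serves every back pain patient seen, not just those who consent, so the first denominator is the more sensible. The spread shows that the allocation rule drives the answer.

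**4. Price year.** Moving amounts to a common price level is indexing. Discounting expresses time preference. Indexing both cohorts to one year introduces no artificial difference. Taken literally, discounting over a lag of 1-2 years at an assumed 1-5% would shift the before/after cost ratio by between 1.01 - 1 = 1% and 1.05^2 - 1 = 10%, in favour of the later cohort.

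**The case against.** The cost lists are not declared exhaustive: Objectives gives examples, Secondary outcome measures says what costs will include, and a condensed article may leave costing detail to a fuller document. This stands to the extent that the omission does not prove delivery will be charged at zero. It does not remove the point, because the article fixes a calculation rule and a costing window, and neither can take in training.

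Part of the intervention's cost is counted. Medium-risk patients are all referred to physiotherapy, with roughly two to four visits, and high-risk patients follow a similar course; those visits are costed. That is correct and limits the gap to delivery.

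A reader might infer that the plan totals direct costs only. The documents do not support this. Objectives, Secondary outcome measures, Table 4 and Table 5 all include indirect costs, and the national register is named as the source for sick-leave payments. The sentence in Statistical methods describes health care resource use, which sick leave is not. A direct-only total would in any case leave out the work-disability savings the investigators expect and so work against a cost-saving result. It cannot be added to the bias described here.

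A reader might also infer that discounting will distort the comparison. No discount rate is given, and the reference to a price level suggests that indexing is meant. The verb is wrong; a biased calculation is not established.

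**Conclusion.** The point holds for delivery costs. Followed as written, the plan gives a before/after cost difference that is not net of the intervention and is biased towards savings. It cannot support the stated assumption that the approach saves costs.

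The 2,532 hours follow from the article's own figures under full attendance. The euro figures do not: about EUR 4-51 per patient rests on the assumed wage, attendance and 3,000 patients. The article gives no expected cost difference to set this against, so it cannot be said that the sign of the result would change. Cost-effectiveness is a stated aim, but costs are secondary outcomes and the primary PROMIS comparison is untouched. The price-level sentence needs a wording correction only.

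**What to change.** In Secondary outcome measures and Table 4, add an intervention delivery cost item: staff and trainer time in training, boosters and mentoring, taken from attendance lists, plus booklets. Allocate it over the low back pain patients seen in each region, state the allocation period, vary it in a sensitivity analysis, and report the cost difference with and without the item. Reconcile the nurse training time between Table 2 and Professional level, since it feeds this item.

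In Statistical methods, replace the discounting sentence with something like: resource use in both cohorts is valued with one unit-cost list for a single price year; register amounts are price-indexed to that year; no discounting is applied within 12 months. A short statement of how the indirect costs already planned enter the comparison would help, with disability pensions named consistently in the text and in Table 4.

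The price is attendance logging, a little costing work, and a less favourable savings figure.
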